### Study Design

The study design rests on a five-arm, randomized, controlled trial with four treatment arms and one control group. With the support of the Burkinabe Ministry of Health and local health centers, HIV patients have been screened and recruited at 80 health care facilities that provide antiretroviral therapy across the 13 regions of Burkina Faso. Using a 7:7:7:7:10 allocation ratio, patients are randomized to one of the five-arms with the control group being slightly oversampled as we introduce two types of control groups; a control group of patients drawn from health centers which do not receive any of the interventions and a spillover-prone control group drawn from health centers which are visited by both treated and untreated patients. A member of the international survey team carried out the randomization in Stata. The team member did not have any interactions with patients. Once patients were randomly allocated, the intervention was launched and the SMS messages are sent. Patients in each of the five groups receive the public standard care but only four groups receive an SMS reminder that varies by the type of message (text versus American standard code for information interchange (ASCII) image) and its frequency (weekly vs semiweekly). The study collaborates with the health care personnel attending to the patients as well as the associations and self-help groups that provide psychosocial support to PLHIV. The former provide medical information and the latter carry out the survey interviews. The health personnel and the enumerators are not informed about the outcome of the random allocation of the participants. Because they do not know which patient is in which group, we do not expect bias. The study will keep track of the patients 6, 12, and 24 months after the intervention is launched.

### Facilities Selection

The investigation will be implemented in health facilities across the 13 regions of Burkina Faso. The health centers are selected from a total of 100 registered facilities that are recorded in the documents of the CNLS-IST as providers of antiretroviral therapy across the 13 health care regions of Burkina Faso [34]. To be eligible to participate in this study, health centers need to fulfill two conditions. First, they need to exist and they need to be functioning. While this sounds like a straightforward requirement it is possible that despite being registered, facilities might have never become operational or have shut down. Second, the health centers need to be willing to collaborate. Specifically, we enrolled a total of 80 health centers with an intended average of 40 patients being recruited per center depending on the eligible population of PLHIV who frequent the health center. To avoid under or overrepresentation of a particular health center, eligible facilities must meet a minimum number of 15 HIV patients and are allowed to enroll a maximum number of 150.

### Participants

#### Eligibility and Informed Consent

The participants need to fulfill five conditions. As an initial step for eligibility, participants must be enrolled in an ART program in 1 of the health care centers collaborating in the study. Second, each patient must provide written informed consent confirming their participation in the study. The informed consent includes signed permission to consult their medical records over the duration of the study. Third, participants must be older than 15 years because the focus of the study is on adult PLHIV. Fourth, participants who have been under ART for less than 4 years are preferred, although, experienced patients are also included. We aim at assessing differential effects for individuals initiating ART versus individuals who have been under treatment for a long time. Because the existing literature suggests that drop-out is highest among those initiating treatment, we place more emphasis on individuals who have recently started ART. Therefore, we aim that at least two-thirds of the sample consists of patients that have been under ART for less than 4 years. We trained and informed the health centers and enumerators about this sampling feature. We requested to be informed (by phone) in the case that patients were included, that have been longer on ART. Thus, from the central level we closely monitored the oversampling of patients, who have been under ART for less than 4 years. Fifth, patients must have reliable access to a mobile phone including a stable network connection. Access to a mobile phone is not a major bottleneck: according to the World Factbook there were 12.5 million subscribers in Burkina Faso in 2014, 68 of 100 inhabitants have a mobile phone, and there are 3 major mobile networks that reach out to the entire country [39,40].

#### Recruitment

The recruitment period lasted for 4 months because patients return to the health centers to refill their stock of antiretroviral medication at different intervals. This time period has been sufficient to reach the target sample size of 3800 individuals.

### Randomization

Randomization was undertaken after the collection of the baseline data. As a first step we randomly identified 8 pure control health centers using the random number generator in Excel. These pure control centers allow us to assess whether there are within health center spillovers from those who receive reminders and those who do not. Across the 72 remaining health centers, we randomly assign individuals to 1 of 5 groups (ie, 1 of 4 treatment packages or the control group of patients who do not receive any text message). Due to the potentially large heterogeneity of patient socioeconomic profiles and variations across health centers, the study applies covariate balancing across multiple baseline covariates to minimize imbalance between treatment groups. To increase statistical power and the precision of the results, participants are ordered along key characteristics and randomized within these ordered blocks. The following characteristics are included in the ordering: gender, age and weight of the participant, duration under antiretroviral treatment, health center identifiers, the reported distance to the health center, CD4 counts, and subjective health rating. Following this 2-step procedure, participants are randomly assigned to 1 of 5 groups (4 of which receive various packages of SMS reminders and a control group, which does not). Thus, there are 2 control groups. One control group consists of individuals who do not receive messages but are affiliated to health centers where others receive messages and a pure control group, which consists of individuals who do not receive messages and are affiliated to the 8 pure control health centers where no one receives a message. The introduction of 2 types of control groups is motivated by a desire to address potential spillovers/contamination between treated persons (those who receive a SMS text message) and patients in the control group (those who don’t receive the SMS text message) but frequent the same health center. We know that medical interventions such as deworming and cancer screenings have spillovers [41,42], similarly voter awareness and cash transfer programs have spillovers to untreated but close populations [43,44]. Having 2 control groups allows us to address whether both treated and untreated patients in the treatment health centers are covered by the intervention [43]. In the analysis, we will introduce a dichotomous variable for control patients from mixed-treatment control sites to assess whether their outcomes differ compared with patients from pure control sites who are unlikely to experience spillovers.

### Intervention

The intervention comprises 4 treatment groups and 1 control group to investigate the impact of different types of SMS text message reminders sent out at different frequencies on patient outcomes. For groups 1 to 4, messages will be sent on a weekly basis. Patients of each of the 4 treatment groups will receive at least 1 text or image message per week. Image messages are used to ensure that the intervention reaches out to people with limited literacy skills and they will be sent as ASCII pictures. Because we do not expect the participants to have smartphones, we use ASCII images that can be displayed on basic mobile phones. The content and frequency of the messages will vary for each of the 4 treatment groups. While the first treatment group will receive only 1 text message per week (low frequency), the second treatment group receives a total of 2 text messages per week (high frequency). Meanwhile, the third group will get 1 text and 1 image message per week and, the fourth group will receive 2 image messages per week. All messages will be sent at 8 am and patients will not be prompted to respond. The impact of the treatments will be assessed in follow-up surveys at 6, 12, and 24 months after the start of the intervention. A detailed identification of the 5 groups, type of interventions, and timings are presented in Table 1.

**Table 1 table1:** Identification of the five intervention groups.

Treatment arms		Intervention (per week)	Timing
**Control group**			
	Eight pure control health centers	No text nor image messages	
	Individuals from the remaining 72 centers randomly allocated to the control group.		
Treatment 1: text-only, low frequency		One text message	Every Monday at 8 am
Treatment 2: text-only, high frequency		Two text messages	Every Monday and Friday at 8 am
Treatment 3: text and image		One text message; one image message	Text: every Monday at 8 am; image: every Friday at 8 am
Treatment 4: image only		One message	Every Monday at 8 am

Furthermore, text messages are sent in French or 1 of the local languages (Moore, Jula, Gulmancema, Fulfulde, or Dagara). The baseline survey determined the main language of each participant to be used in the text messages. The content of the text messages will vary to ensure that the participants remain curious about the messages over the study period. We are concerned that individuals stop looking at an identical message after some time as they already know the content of the standardized message. Furthermore, we opted for a mix of messages instead of standardized messages due to concerns about exclusively “negative” framing (Textbox 1). However, we acknowledge that this approach does not allow us to systematically compare the implications of standardized messages across different treatment arms. Figure 1 shows two examples of the ASCII images that are sent.

Examples of the text messages that are sent.
*Hello. Do not forget to take your pills.*

*Your health is important. Take your pills.*

*You are very important. Do not play with your health. Take your pills.*

*Are you very busy? This is why I remind you to take your pills.*

*Don’t forget that you are strong, unique, funny and blessed. You are needed. This is why I would like to remind you to regularly take your pills.*

Patients in the control group do not receive any text messages but only the standard care. Along with periodic clinical check-ups and treatment counseling, this includes routine monitoring of patient CD4 cells as measure of disease progression. Adherence support and/or additional treatment counseling may also be provided at the community level. This will be assessed during follow-up surveys.

**Figure 1 figure1:**
[figure not shown]
Examples of ASCII images used in the intervention.

### Sample Size

Power calculations need to account for the stratified nature of the sample. There are 80 treatment centers. We randomly preserve 8 pure control centers to assess spillovers. Within each of the remaining 72 centers, treated and untreated participants are sampled. Thus, for the majority of the centers treatment allocation is not at the level of the center but at the level of the individual. The sample size is calculated with the clustersampsi command of Stata, Version 13 assuming a power of 80% and a significance level of 5%. Furthermore, we impose an intraclass correlation coefficient of 0.015 to quantify the degree to which patients within the same health center are related [45]. We allow for cluster sizes to vary because we know that the size of the eligible population varies across clusters. Thus, we impose a coefficient of variation of cluster sizes of 0.5 (ratio of the standard deviation of cluster sizes to the mean cluster size). Because we collect baseline information we can control for observable characteristics and their correlation with the outcome. We impose a correlation of 0.85. Lastly, because we expect that 35% of the patients will forget to take antiretroviral (ARV) medication from time to time, a target sample size of 3800 PLHIV is needed to obtain a “minimum detectable effect” of an increase in adherence from 65% to 70%. These adherence figures are based on a reported 67% adherence among female PLHIV in Burkina and the government target to bring adherence up to at least 80% [37,38]. As we are conservative about the possibilities of mHealth to raise adherence by 15% the sample was set up in such a way to also identify small gains.

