### Study Measures

#### Primary Outcomes

The study focuses on the measurement of three primary outcomes: retention in care, adherence to ART, and disease progression. Retention is measured by a dichotomous variable-whether a patient remains on ART 6, 12, and 24 months after the intervention has started as compared with baseline [46,47]. Retention could have been conceptualized also as the incidence or number of missed visits during a given reference period [48]. However, remaining in care is in itself an important challenge in Burkina Faso. This is in stark contrast to the situation of PLHIV in developed countries. Therefore, we decided to choose remaining on an ART regimen as our retention measure. Adherence or rather lack of adherence to ART is evaluated as the number of doses missed in the past 7 days, which is a self-reported measure [49-51]. It may have been better to use actual pharmacy dispensing data to calculate a medication possession ratio. However, our field experience suggested that it was not always feasible to obtain detailed and correct information about pharmacy dispensing. Contrary to developed countries where standards across hospitals may be similar, in Burkina Faso we observed considerable differences in the standards and routines across health centers both between regions and within them. Because we assess a wide-scale intervention our study also includes rural and remote areas, which are perhaps even less capable of providing this information. Therefore, we opted for inclusiveness knowing that this implies adjustments in the type of comparable indicators that can be collected and analyzed across health centers [51]. Lastly, disease progression is analyzed using patients’ CD4 counts.

Information on these primary outcomes will be collected using individual questionnaires and patient medical records. Table 2 presents details about the indicators with information about the date of data collection.

**Table 2 table2:** Primary and secondary outcome variables.

Classification		Indicators/measures	Baseline	Follow-ups (months after)		
				6	12	24

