### Analysis Plan

Our analysis will exploit the randomized nature of the intervention to attribute treatment effects. In addition to a simple comparison between the pooled treatments and the control group we will also assess the differential impact of the 4 treatment arms. We will employ multivariate regression models to assess the impact of the interventions on each of the primary outcome variables. For the continuous outcome measure (CD4 count) we plan to employ an Ordinary Least Squares model. For the count data (pill doses missed) and if the continuous outcome measure is skewed, we propose to make use of a Poisson model; for the dichotomous outcome (remaining on ARV regimen), we propose to employ a Logit model. In all models we will control for the clustering of participants within health centers.

We will make use of the coefficient estimates from the 4 treatment arms to establish a preference ordering of the effectiveness of the different types (text vs ASCII image) and frequencies (weekly vs semiweekly) of the SMS text message reminders. We will also estimate quantile regressions to identify which group(s) of participants are most (least) likely to have gained from the interventions. Comprehensive data on patient characteristics collected at baseline will allow us to control for confounding factors and patient heterogeneity. These patient characteristics include age, gender, ethnicity, education, whether the patient is the head of the household, income, and whether the patient works. The simple comparison of outcome variables across groups will be complemented by a difference-in-difference identification strategy where we jointly employ the data from the three follow-up surveys. This analysis will permit us to tease out the differences in health outcomes attributable to each of the 4 interventions while controlling for time-fixed effects.

The data will be collected and coded by trained enumerators and analyzed using the statistical and data analysis program STATA. We will use conventional levels of significance at 1%, 5%, and 10%. Because we identified three primary outcome variables we will make use of an inflated alpha when determining significance levels for each and every outcome separately. We apply this correction because the more significance tests we conduct at α=0.05, the more likely we are to claim that we have a statistically significant result. For a significance level of 5% the Bonferroni inflated alpha is 0.05/3 = 0.015.

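### The stated 80% power is for a yes/no adherence rate at alpha 0.05, while the plan tests a missed-dose count at 0.05/3, so no planned primary test is shown to have it

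*Protocol article*

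**What the plan says.** The Sample Size section of the protocol article reports a calculation made "assuming a power of 80% and a significance level of 5" per cent. It starts from a proportion: "we expect that 35% of the patients will forget to take antiretroviral (ARV) medication from time to time". On that basis "a target sample size of 3800 PLHIV is needed" to detect "an increase in adherence from 65% to 70" per cent. The other inputs are an intraclass correlation of 0.015, a coefficient of variation of centre size of 0.5 and a correlation of 0.85 with baseline information. The section does not say which groups are compared, whether the test is two-sided, or what mean centre size was used.

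Under Primary Outcomes, adherence is "evaluated as the number of doses missed in the past 7 days, which is a self-reported measure". The Analysis Plan assigns this count to a Poisson model. It also says that, because there are three primary outcomes, "we will make use of an inflated alpha when determining significance levels for each and every outcome separately", and prints the level as 0.05/3 = 0.015. Two kinds of comparison are planned: all messaging arms pooled against control, and the four arms separately, which are then ranked by their coefficients. Study Design gives the allocation as 7:7:7:7:10. Facilities Selection states "we enrolled a total of 80 health centers with an intended average of 40 patients being recruited per center".

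**The concern.** The power statement and the analysis differ in two ways: the significance level (0.05 against 0.05/3) and the endpoint (a proportion against a count). A reader who takes the 80% at face value would treat a null arm-level result as good evidence against a five-point gain in adherence. Arm-level results matter here, because the main objective is the impact of four message packages and the plan ranks them. For the count that will be analysed, and for retention and CD4 count, the article gives no power figure.

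**Working it through.** **Inputs from the article.** p0 = 0.65, p1 = 0.70, alpha 0.05, power 80%, ICC 0.015, CV 0.5, r = 0.85, N = 3800, 80 centres. The allocation gives 3800 × 7/38 = 700 per messaging arm, 3800 × 10/38 = 1000 controls and 2800 pooled.

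**Assumptions the article does not state.** Two-sided test; baseline correction of the form 1 − r²; mean centre size 3800/80 = 47.5; pure and mixed-centre controls counted as one group of 1000.

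**Step 1: reproduce the stated size.**
- Individual n per arm = (1.960 + 0.842)² × (0.65×0.35 + 0.70×0.30)/0.05² ≈ 1374.
- Design effect = 1 + ((1 + 0.5²)×47.5 − 1)×0.015 = 1.876.
- Baseline correction = 1 − 0.85² = 0.2775.
- Combined factor F = 1.876 × 0.2775 = 0.5205.
- n per arm = 1374 × 0.5205 ≈ 715, against 700 available.

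This fits an equal-arm comparison. A single two-group comparison would need only 2 × 715 = 1430, far below 3800. The fit supports the arm-level reading but does not prove it.

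**Step 2: change only alpha.** SE = √[F × (0.2275/n0 + 0.2100/n1)] and power = Φ(0.05/SE − z), with z = 1.960 at 0.05 and 2.394 at 0.0167. The detectable difference at 80% power is (z + 0.842) × SE.

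| Contrast | SE | Power at 0.05 | Power at 0.0167 | Detectable difference at 0.0167 |
|---|---|---|---|---|
| Arm v arm, 700 v 700 | 0.01804 | 79% | 65% | 5.8 points |
| Arm v control, 700 v 1000 | 0.01657 | 86% | 73% | 5.4 points |
| Pooled v control, 2800 v 1000 | 0.01255 | 98% | 94% | 4.1 points |

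At the printed 0.015 (z = 2.432) the powers are 63%, 72% and 94%.

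**Step 3: sensitivities at 0.0167.**
- *Centre size 40.* The intended average implies 80 × 40 = 3200, not 3800. With 40 the design effect is 1.735, and arm-level power is 69% (arm v arm) and 77% (arm v control).
- *No between-centre inflation (F = 0.2775).* The SEs are 0.01317 and 0.01210, giving 92% (arm v arm) and 96% (arm v control).
- *r = 0.5 in place of 0.85, design effect 1.876.* F = 1.876 × 0.75 = 1.407, giving 24%, 29% and 51% for the three contrasts.

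**Step 4: the count.** The article gives no mean or dispersion for missed doses, so power cannot be derived from it. As an illustration, assume 35% v 30% of patients miss any dose. Among those who miss, scale the control mean to 1, let the CV be c, and let g be the ratio of treated to control mean. The group means are 0.35 and 0.30g; the variances are 0.35(1 + c²) − 0.35² and 0.30g²(1 + c²) − (0.30g)². Use F = 0.5205 again. For c from 0 to 1 and g of 1 or 0.9, power at 0.0167 runs from 26% to 99% for arm v arm and from 55% to over 99% for pooled v control. The 80% could be missed or exceeded.

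**The case against.** **A reader might infer that every primary test falls short of 80%.** The article does not support this. The planned pooled comparison keeps about 94% at 0.0167 for the binary effect. For the count, retention and CD4 count, power is unknown rather than shown to be low.

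**The 65% and 73% may be too pessimistic.** They apply the full between-centre design effect. Yet Sample Size says that in most centres allocation is by individual, and Randomization includes the health center identifier in the ordering used to form blocks. Arm v arm contrasts lie wholly within the 72 mixed centres, where the between-centre component largely cancels. This objection stands: 65–73% is the plan's own method at the adjusted alpha, not a settled figure for this design. The 96% for arm v control is itself approximate, because some controls come from the 8 pure control centres.

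**The powered contrast is inferred.** This also stands. The match of 715 to 700 rests on three unstated assumptions and on equal groups, whereas the allocation favours control.

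**A reader might apply the Introduction's 22.5% discontinuation figure as attrition and lower the power further.** That figure describes stopping ART in reviews of Sub-Saharan Africa. Remaining on ART is itself a primary outcome here, and the Analysis Plan expects missing data below 5%. No such reduction is made.

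**The centre size of 40 is not a clear error.** It is an intended average that depends on the eligible population, and Sample Size names no mean centre size. The point is only that the value used should be stated.

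None of this removes the mismatch in alpha or in endpoint.

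**Conclusion.** The point holds in limited form. The 80% refers to a proportion tested at 0.05; the plan tests a count at 0.05/3, and that level is also misprinted as 0.015. No planned primary test is shown to have the stated power.

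For the binary effect at 0.0167, arm-level power lies between about 65–73% (full design effect) and 92–96% (no between-centre inflation), and pooled v control is about 94% or more. These figures rest on a two-sided test, the 1 − r² correction, the article's r = 0.85 and, for those with the design effect, 47.5 patients per centre. They fall sharply if the correlation is lower. It is established that the statement is wrong as written; it is not established that the trial is underpowered.

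**What to change.** - Correct 0.015 to 0.0167 in the Analysis Plan.
- In Sample Size, name the contrast behind 3800, the sidedness of the test, the form of the baseline correction and the mean centre size used.
- Restate power or the detectable difference at 0.0167 separately for pooled v control, arm v control and arm v arm, with and without the between-centre design effect.
- Keep the missed-dose count as the primary adherence outcome and add its detectable rate ratio, using the mean and dispersion of missed doses from the baseline survey. Report having no missed dose in 7 days only as a supporting analysis. Making it primary now would change an endpoint after follow-up collection began in April 2016, which is more than a change of wording.

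The cost is revised text, a short calculation on baseline data already collected, and a less favourable or more qualified arm-level power statement. No extra patients are needed. The article says that analysis has not started, so the restatement can still be made before results are known.

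### The 80% power statement reproduces at arm level only with an unsourced and implausible baseline-outcome correlation of 0.85, and the powered contrast is not named

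*Protocol article*

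**What the plan says.** The Sample Size section of the protocol article sets out the calculation "assuming a power of 80% and a significance level of 5" percent, for "an increase in adherence from 65% to 70" percent. Its other inputs are:

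- clustering: "we impose an intraclass correlation coefficient of 0.015", with a reference;
- unequal centers: "we impose a coefficient of variation of cluster sizes of 0.5";
- baseline adjustment: "Because we collect baseline information we can control for observable characteristics and their correlation with the outcome", followed by "We impose a correlation of 0.85", with no reference or reason.

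The result is 3800 patients. The section does not say which comparison this number powers. It uses a Stata command for cluster trials, yet notes that "for the majority of the centers treatment allocation is not at the level of the center but at the level of the individual".

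The Analysis Plan describes the adjustment covariates: "These patient characteristics include age, gender, ethnicity, education, whether the patient is the head of the household, income, and whether the patient works". Baseline adherence is not named there, although Table 2 shows that it is collected. The Analysis Plan intends both a pooled comparison with control and comparisons of the four arms.

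**The concern.** A correlation of 0.85 removes 0.85² = 72% of the outcome variance and so cuts the required sample by a factor of 3.6. Nothing in the article supports a value that high. The named covariates are sociodemographic. The outcome is a short self-reported recall, and the Sample Size section itself describes forgetting as occasional.

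The stated 80% is what readers will use to interpret a non-significant result. The main objective concerns four message packages and the Analysis Plan will rank them, so arm-level power matters. If it is well below 80%, a null finding for one package says less than the article implies.

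**Working it through.** **Inputs.** From Sample Size: 65% vs 70%, power 80%, alpha 5% (taken as two-sided), ICC 0.015, CV 0.5, r = 0.85, 80 centers, N = 3800. From Study Design: allocation 7:7:7:7:10, so 700 per SMS arm and 1000 controls. Assumptions of this check: mean center size 3800/80 = 47.5, and the correlation enters as 1 − r².

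**Step 1: reproduce the plan's figure.**

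- Unadjusted n per arm = [1.960·√(2·0.675·0.325) + 0.842·√(0.65·0.35 + 0.70·0.30)]² / 0.05² = 1377.
- Design effect = 1 + [(0.5² + 1)·47.5 − 1]·0.015 = 1.876.
- 1 − 0.85² = 0.2775.
- 1377 × 1.876 × 0.2775 = 717 per arm. Scaled by 38/7 this is about 3891, within 3% of 3800. Power at 700 vs 700 is 79.1%.
- Without the correlation: 1377 × 1.876 = 2583 per arm.

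With the intended 40 patients per center (Facilities Selection), the result is 663 per arm, about 3599 in total. At either center size, r = 0, 0.5 or 0.7 does not return about 3800 for an arm-level contrast.

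**Step 2: what 0.85 implies for a yes/no outcome at 65%.**

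- P(adherent both times) = 0.65² + 0.85·0.65·0.35 = 0.616.
- Adherent patients who lapse: 1 − 0.616/0.65 = 5.25%.
- Non-adherent patients who become adherent: (0.65 − 0.616)/0.35 = 9.75%.
- All patients who switch: 2·(0.65 − 0.616) = 6.8%.

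Baseline recruitment ran from February to May 2015 and the first follow-up began in April 2016. These are therefore 7-day windows about a year apart, and the later waves are further away.

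**Step 3: variance that fits the design.** Within a center, individual randomisation removes the between-center component, so the factor is D = 1 − 0.015 = 0.985. For contrasts with all 1000 controls, the 8 pure-control centers act as clusters. Assuming 8 × 47.5 = 380 patients there:

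- S = 1.25·[72·(0.38/72)² + 8·(0.38/8)²] = 0.02507.
- D = 0.985 + 0.015·S/h, where h = 1/n_SMS + 1/1000.
- One arm: h = 0.002429, D = 1.14. Pooled: h = 0.001357, D = 1.26.

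**Step 4: power for 5 points.** Power = Φ[(0.05 − z·SE0)/SE1]. SE0 uses the pooled proportion, SE1 the separate proportions, and both variances are multiplied by D(1 − r²). Two examples at r = 0 and alpha 0.05:

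- 700 vs 700: (0.05 − 1.960·0.02485)/0.02481 = 0.052, power 52%.
- 2800 vs 1000, D = 1.26: (0.05 − 1.960·0.01919)/0.01954 = 0.634, power 74%.

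The documents give no observed correlation, so r = 0 to 0.5 is assumed, with one wave and no attrition:

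| Contrast | D | alpha 0.05 | alpha 0.05/3 |
|---|---|---|---|
| Arm vs arm (700/700) | 0.985 | 52–64% | 35–47% |
| Arm vs control (700/1000), mixed | 1.14 | 52–65% | 35–48% |
| Arm vs control, individual | 0.985 | 59–71% | 41–55% |
| Pooled vs control (2800/1000), mixed | 1.26 | 74–85% | 58–73% |
| Pooled vs control, individual | 0.985 | 83–92% | 71–84% |

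Other standard normal approximations move these by one or two points. The article prints 0.05/3 as 0.015; the table uses 0.0167.

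**Step 5: other readings.** The correlation needed for 80% at alpha 0.05 is about 0.70 for arm vs arm, 0.69 for arm vs control (mixed) and 0.38 for pooled (mixed). At alpha 0.05/3 and r = 0 to 0.5, single-arm contrasts have 80% power for about 6.4–7.9 points (arm vs arm 6.9–7.9).

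**The case against.** Several points on the other side have force.

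- **The two errors offset each other.** With r = 0.85 and individual randomisation, arm-level power would be about 97%. This stands, but two mismatched inputs that net to about 80% do not support the statement.
- **A reader might infer power as low as 31% for an arm.** That figure comes from 700 vs 700 at r = 0 with the full 1.876 inflation. It does not fit arms randomised within the same centers, so it should not be used.
- **A reader might infer that 0.85 is impossible.** The documents do not show that. The covariate list is introduced as examples, baseline missed doses are collected, a difference-in-difference analysis is planned, and randomisation is blocked on several characteristics. With margins of 65% and 70% the largest attainable correlation is √(0.65·0.30/(0.35·0.70)) = 0.89. Unsourced and implausible is as far as the evidence goes.
- **A reader might infer that 80% is false for every contrast.** It is not. Pooled SMS vs control, the first comparison named in the Analysis Plan, is near or above 80% at alpha 0.05 without the 0.85.
- **The analysis will use three follow-up waves jointly.** Averaging them multiplies the variance by (1 + 2c)/3, where c is the within-patient correlation. For an assumed c of 0.3 to 0.7 (factor 0.53 to 0.80), D = 0.985 and no baseline adjustment, power is about 61–79% for arm vs arm and 68–85% for arm vs control. This helps an average effect, not the wave-specific effects needed to study fatigue.

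What remains is that the stated figure depends on one unsupported input, and that arm-level power at a single wave is below 80% for any correlation up to 0.5.

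**Conclusion.** The point holds as a misstatement of the power basis. It does not show that the trial is underpowered throughout. The 80% reproduces at arm level only with r = 0.85, under the assumed reading of a 1:1 pair of 700, 47.5 patients per center and factor 1 − r².

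On assumptions that fit the design, single-arm contrasts fall clearly short at one wave. The pooled contrast is the best supported, but at the adjusted alpha it reaches 80% only in the upper part of the individual-variance range. These percentages depend on r = 0 to 0.5, on about 380 patients in the pure-control centers for the mixed rows, and on no attrition; losses would lower them. How a null arm result would be reported is conjecture, so it does not add to the finding.

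**What to change.** In the Sample Size section:

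1. Give a source for 0.85 that matches this outcome and interval, or remove it.
2. Name the contrast that 3800 is meant to power.
3. Restate power and minimum detectable effect for pooled vs control, each arm vs control, and arm vs arm. Use a variance for individual randomisation in 72 centers plus 8 pure-control clusters, r from 0 to 0.5, and the adjusted alpha of 0.05/3.
4. State that single-arm contrasts detect about 6–8 points at that alpha, and that the pooled contrast is the best supported but reaches 80% only under some of these assumptions.

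In the Analysis Plan, add baseline missed doses to the adherence model. They are already collected, and they are the most direct way to gain precision.

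The cost is wording and one added covariate. The stated power becomes less favourable. Recruitment is complete, enrolment does not change, and the article reports that analysis has not begun.
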